#### Analysis plan

In cluster randomized controlled trials with relatively few clusters, it is recommended to assess the effectiveness of randomization as a first step. Therefore, we will first examine the balance of baseline characteristics of the health centre clusters and the individual patients across intervention groups. Analyses will be done at both cluster (health centre) and individual (health care worker) levels, adjusted for clustering. At the health centre level (cluster level), we will use multivariable linear regression to compare mean staff satisfaction, staff retention and total staffing, adjusting for potential confounders. At the health worker level (individual level), multivariable regression adjusted for clustering by health centre will be used to compare HCW satisfaction scores. For this analysis, we will only include those HCWs who complete a survey at baseline and the appropriate outcome time point and are working in the same health center. Cox regression modeling will be used to estimate the survival probabilities of health care workers (proportion of days employed at health centre over two years of follow-up) to compare 'survival' (sustained days of work at same health centre) across intervention groups, adjusting for potential confounders. Health centre level analyses will use multivariable linear regression to compare secondary outcomes such treatment initiation (ARV, cotrimoxazole, TB, malaria etc.). Treatment initiation will be calculated as the number of patients placed on "X" treatment over the denominator of "Y" health centre referral population. To adjust for cluster randomization, we will use generalized estimating equation binomial regression models with log link and exchangeable correlation structures to estimate the relative risks (RR) and 95% confidence intervals for 'survival' rates (proportion of days employed at health centre over two years of follow-up) between the intervention group (receive PALM PLUS) with the control group as a reference. SAS version 9.2 (SAS Institute Inc, 2008) will be used for all analyses. All analyses will be conducted using the intention to treat principle.

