Attention to the quality of clinical care provided for HIV/AIDS and other primary care conditions while increasing access to HIV/AIDS services is also important. This is especially so since the workload inherent in a scale-up of access to HIV/AIDS services may have unintended negative consequences on existing primary care services in those same centers [3,5]. This study will test an adapted clinical guideline and training approach, Practical Approach to Lung Health and HIV/AIDS in Malawi (PALM PLUS), to strengthening the health care workforce in a primary care setting where HIV/AIDS services are being decentralized. PALM PLUS is designed to support mid-level HCWs, i.e. nurses and non-physician clinicians (in Malawi, medical assistants and clinical officers), with the overall goal of improving equitable access to quality HIV/AIDS care and primary care services. The primary objectives of the intervention are to improve mid-level HCW retention in rural health centres and improve their job satisfaction; secondary objectives are to improve patient outcomes. Our hypotheses are that the PALM PLUS intervention will be associated with: 1) improved staffing and staff satisfaction, and 2) improved patient outcomes.

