### Outcome measures

Our primary outcomes will be measured at the cluster (health centre) and individual (staff) levels and relate to clinical staffing (clinical officers, medical assistants, nurses): 1) retention (staff continuing to work in same health centre), 2) total staffing (total of retention/recruitment/loss), and 3) staff satisfaction at the cluster and individual level. Secondary outcomes are clinical outcomes targeted by the PALM PLUS guideline measured at the health centre level: 1) total patient visits, 2) use of cotrimoxazole prophylaxis among HIV+ pregnant women, 3) HIV testing among pregnant women, 4) ART provision among HIV+ pregnant women, 5) Non-ART prevention-of-mother-to-child-transmission treatment provided to HIV+ pregnant women, 6) new adult ART initiations, 7) new adult TB treatment initiations, 8) new adult TB treatment initiations among ART patients, 9) new HIV diagnosis among TB patients, 10) new ART initiations among TB patients, 11) administration of malaria treatments. We will also evaluate competing pediatric primary health priorities as potential unintended consequences (since PALM PLUS targets only the care of adults): 1) total and measles-specific immunizations given 0-5yrs, 2) new ARV initiations among children, 3) HIV tests among children.

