#### Sample size Calculations

At a two-sided alpha of 0.05 and holding power at 80%, using an estimated value for the intracluster correlation coefficient (ICC) of 0.15, and p1 of 0.90 and p2 of 0.65, an inflation factor of 0.15 and an average cluster size of 5 workers then 67 workers will be required per study arm (the sample size unadjusted for clustering is 42 workers). Inflating this by 10% to ensure a sufficient number of staff have completed multiple longitudinal satisfaction surveys within the same health center, brings the required sample to 74 workers which is equivalent to needing 15 clusters (health centers) per study arm. Rationale for ICC: The ICC is almost always unknown prior to conducting a study. In this instance we have chosen an estimate for the ICC to be 0.15. The rationale for the selection of this ICC value is that previous studies have shown higher ICC values for process variables (e.g., health worker days) compared to outcome variables in the primary care setting [9] and in a previous study which summarized the median ICC from several studies using process variables, the median was found to be 0.2 [10].

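### The individual-level satisfaction analysis keeps only staff who stay in the same centre, so it conditions on retention, is not intention to treat, and may outrun the 10% allowance

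*Protocol article*

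**What the plan says.** The protocol article bears on this point in four places.

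- **Outcome measures.** One primary outcome is "retention (staff continuing to work in same health centre"); another is "staff satisfaction at the cluster and individual level". The Introduction gives the primary objectives as to "improve mid-level HCW retention in rural health centres and improve their job satisfaction".
- **Analysis plan, who is analysed.** Satisfaction is compared twice. A centre-level linear regression compares mean satisfaction, with no restriction on who contributes. A worker-level regression adjusted for clustering will "only include those HCWs who complete a survey at baseline and the appropriate outcome time point and are working in the same health center".
- **Analysis plan, principle.** The section closes: "All analyses will be conducted using the intention to treat principle".
- **Sample size Calculations.** The calculation uses "p1 of 0.90 and p2 of 0.65", without saying which outcome, arm or time they refer to. It reaches 67 workers per arm after clustering, and then: "Inflating this by 10% to ensure a sufficient number of staff have completed multiple longitudinal satisfaction surveys within the same health center". That gives 74 workers, or 15 centres per arm.

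**The concern.** The rule for entering the worker-level analysis is an event after randomisation: still being in post in the same centre and answering a second survey. Remaining in post is itself a primary outcome, and the trial is designed in the expectation that it will differ by arm. If it does, the arms are filtered to different degrees before satisfaction is compared, and randomisation no longer protects the comparison. The trial is also unblinded, so survey completion may differ by arm too.

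The protocol applies the right logic elsewhere. Under potential confounders at the cluster level, the number of training sessions is kept out of the primary analysis because it arises after randomisation. Staying in post arises after randomisation as well, yet it decides who is counted.

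Two things are at stake. If less satisfied staff are likelier to leave, the arm with better retention keeps more of them, and its mean among stayers is pulled down relative to the other arm. And the number of workers available for this primary outcome may fall below the number the protocol says it needs.

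**Working it through.** **1. Reproducing the sample size.** Inputs from Sample size Calculations: 0.90 vs 0.65, two-sided alpha 0.05, power 80%, ICC 0.15, 5 workers per centre.

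- Two-proportion formula without continuity correction: 43 per arm (stated 42, within rounding of method).
- Design effect 1 + (5 - 1) x 0.15 = 1.6; 42 x 1.6 = 67.2 (stated 67).
- 67 x 1.10 = 73.7, so 74 as stated; 74 / 5 = 14.8, so 15 centres, which hold 75 workers.

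The arithmetic is sound. The question is whether 10% covers the loss that the restriction creates.

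**2. Expected stayers.** This step assumes that p1 and p2 are retention. Retention is the primary outcome most naturally expressed as a proportion, and the ICC rationale mentions health worker days, but the section does not say so. The late survey is at 10-12 months, while the Analysis plan follows retention over two years, so two readings are shown. For two-year rates with a constant hazard, 12-month retention is the square root: 0.949 and 0.806.

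| Reading of 0.90 / 0.65 | Loss by late survey | Mean loss | Stayers of 75 | Needed in lower arm for 67 |
|---|---|---|---|---|
| Retention at late survey | 10% / 35% | 22.5% | 67.5 / 48.8 | 67 / 0.65 = 103.1, so 104 |
| Two-year retention | 5% / 19% | 12.3% | 71.2 / 60.5 | 67 / 0.806 = 83.1, so 84 |

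A third reading, the mean proportion of days employed over two years with constant hazard, gives 67.4 and 47.0, close to the first row. All figures precede survey non-response. With an assumed 90% response, the first row becomes 60.8 and 43.9.

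**3. Size of the selection effect.** Assume no true effect on satisfaction, and a normal tendency to stay that correlates rho with the satisfaction score. The mean score among stayers, in SD units, is rho x phi(z) / P, where P is the proportion staying, z the normal quantile of P and phi the normal density.

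- Late-survey reading: factors 0.1950 (P = 0.90) and 0.5698 (P = 0.65), difference -0.3748. For rho 0.2, 0.3 and 0.5: -0.07, -0.11 and -0.19 SD.
- Two-year reading: factors 0.1110 and 0.3407, difference -0.2297. For the same rho: -0.05, -0.07 and -0.11 SD.

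The sign is against the better-retained arm. The values of rho are assumptions; the protocol gives none.

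**4. With the baseline score in the model.** Assume a baseline to follow-up correlation of 0.5 and equal correlation of both scores with staying. Under the late-survey reading, simulation of a baseline-adjusted comparison leaves about -0.04, -0.06 and -0.10 SD. A change-score comparison leaves about zero, because the selection shifts both scores equally. If leaving follows the later score more than the baseline one, less of the bias is removed.

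**5. Precision.** Detectable difference = (1.960 + 0.842) x sqrt(DE1/n1 + DE2/n2). With a design effect of 1.6 throughout, 67 per arm gives 0.61 SD, and 67.5 vs 48.75 gives 0.67 SD. If the design effect shrinks with the number of stayers per centre (4.47 in both arms, against 4.5 and 3.25), the change is from 0.60 to 0.63 SD.

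**The case against.** The strongest reply is that the restriction touches only one of two satisfaction analyses. The centre-level comparison of means has no such rule, and neither do the Cox and binomial models for retention. That is correct, and a reader who inferred that the satisfaction outcome as a whole, or the retention result, is compromised would go beyond the text. It does not repair the worker-level analysis, which serves a named primary outcome.

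A second reply is that the sizes rest on assumptions. This also stands. The protocol does not label p1 and p2, so it does not say that 35% of an arm will leave. Under the two-year reading the mean loss of 12.3% is close to the 10% allowance, and total stayers (71.2 + 60.5 = 131.7) nearly reach 2 x 67 = 134; the gap is then mainly in one arm. The bias needs satisfaction and staying to be related. The Discussion lists factors it thinks may affect both, but gives no strength. Baseline adjustment reduces the bias further, and the 2-4 month survey would lose fewer staff.

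Third, a reader might infer that a real benefit would be reversed. Under the assumptions above, that needs a true benefit smaller than 0.19 SD, well below the roughly 0.6 SD that the trial could detect. Attenuation is the supported claim.

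Fourth, 67 comes from a binary comparison and is not a power calculation for a satisfaction score. The shortfall is against the protocol's own target, and the loss of precision is modest.

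Last, satisfaction with a post that someone has left is hard to define, and movers may land in a centre of the other arm. For that reason the fix does not depend on surveying movers or on scoring leavers as unfavourable.

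**Conclusion.** The structural point holds whatever the numbers. A primary outcome is analysed in a set defined by another primary outcome that the intervention targets, under a heading that promises intention to treat for everything. This is a stated rule, not detail left to an analysis plan.

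The size is uncertain and moderate. For assumed correlations of 0.2 to 0.5, the spurious difference runs from about -0.07 to -0.19 SD (late-survey reading) or -0.05 to -0.11 SD (two-year reading). It is smaller with baseline adjustment, and near zero for change scores if staying relates equally to both scores.

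The conflict with the 10% allowance is conditional on p1 and p2 being retention. Given that, the less-retained arm falls below 67 under each reading tried, by about 18 workers at the late-survey reading and about 7 at the two-year one, before non-response.

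**What to change.** In the Analysis plan:

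- Make the primary worker-level satisfaction analysis a mixed model in all workers with a baseline survey, assigned to the centre as randomised. Use every available baseline, 2-4 month and 10-12 month score, with clustering by centre. Staff who leave later then contribute the scores they gave.
- Add a sensitivity analysis for departures from missing at random.
- Keep the same-centre completer set as a supportive analysis, labelled as a comparison of stayers and not as intention to treat.

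In Sample size Calculations, label p1 and p2 by outcome and time, and replace the 10% statement with the evaluable numbers per arm that follow. Enlarging the trial is not a ready option, because all 30 eligible centres in the district are already included.

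The cost is a little more analysis work and a less favourable stated evaluable number. A missing-at-random assumption remains, most plainly for staff who leave before the 2-4 month survey and so have only a baseline score.

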**Methods/Design:**

A cluster-randomized trial design is being used to compare usual care with a standardized clinical guideline and training intervention, PALM PLUS. The intervention targets middle-cadre health care workers (nurses, clinical officers, medical assistants) in 30 rural primary care health centres in a single district in Malawi. PALM PLUS is an integrated, symptom-based and user-friendly guideline consistent with Malawian national treatment protocols. Training is standardized and based on an educational outreach approach. Trainers will be front-line peer healthcare workers trained to provide outreach training and support to their fellow front-line healthcare workers during focused (1-2 hours), intermittent, interactive sessions on-site in health centers. Primary outcomes are health care worker retention and satisfaction. Secondary outcomes are clinical outcomes measured at the health centre level for HIV/AIDS, tuberculosis, prevention-of-mother-to-child-transmission of HIV and other primary care conditions. Effect sizes and 95% confidence intervals for outcomes will be presented. Assessment of outcomes will occur at 1 year post- implementation.

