### Ascertainment of outcomes

Outcomes will be ascertained at baseline and during monthly visits to all health centers; main comparison will be at 12 months vs. baseline;. The clinical manager will be interviewed each visit to determine ongoing employment, and dates of new arrivals and departures of clinical staff. A validated staff satisfaction survey [8] will be administered to clinical staff (at baseline, 2-4 months [for immediate staff satisfaction/retention evaluation], and 10-12 months [late outcomes], ensuring that data is collected for approximately the same calendar months at study and control sites. Patient outcomes will be determined by monthly review of health centre registers and/or patient treatment cards.

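### Individual-level retention is analysed over two years while the main comparison is set at 12 months, and the sample-size proportions carry no time point

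*Protocol article*

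**What the plan says.** All places are in the protocol article.

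- **Outcome measures.** Retention is the first primary outcome listed: "1) retention (staff continuing to work in same health centre". The definition has no time point.
- **Abstract, Methods/Design.** "Assessment of outcomes will occur at 1 year post- implementation".
- **Ascertainment of outcomes.** The "main comparison will be at 12 months vs. baseline". Employment status and arrival and departure dates come from monthly visits, for which no end is stated. The last satisfaction survey is at "and 10-12 months [late outcomes".
- **Analysis plan.** Retention is analysed in three ways. The first is a cluster-level multivariable linear regression with no stated window. The second is a Cox model for individual workers. The third is a GEE binomial model with log link that yields a relative risk. The Cox and GEE measures are both described as "proportion of days employed at health centre over two years of follow-up".
- **Sample size calculations.** "At a two-sided alpha of 0.05 and holding power at 80" per cent, the inputs are "p1 of 0.90 and p2 of 0.65", an ICC of 0.15 and an average of 5 workers per cluster. The results are 42 workers per arm unadjusted, 67 after clustering, 74 after a 10% addition, and 15 centres per arm. Neither the outcome nor the time point behind the two proportions is named.

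**The concern.** Two horizons are fixed for one primary outcome and nothing reconciles them. The two-year window appears twice, so it is harder to dismiss as a single slip. It sits in the only individual-level models for retention. No sentence calls that analysis secondary or an extension, and none says that collection runs to month 24.

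The trial is unblinded and departure dates accrue monthly. If the horizon stays open, the retention contrast that is reported could be settled after the data have been seen. If collection does end at 12 months, a two-year denominator cannot be filled. If it runs to 24 months, the abstract is incomplete. In addition, the stated 80% power cannot be attached to a time point.

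**Working it through.** **1. Reproduce the plan's own figures.** The formula is the pooled two-proportion one, two-sided 0.05, 80% power:

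n = [1.96·√(2·p̄·(1−p̄)) + 0.8416·√(p1(1−p1) + p2(1−p2))]² / (p1−p2)²

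With 0.90 and 0.65, p̄ = 0.775, and n = [1.96·√0.34875 + 0.8416·√0.3175]² / 0.0625 ≈ 42.6. That is 43 rounded up; the plan has 42.

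- Design effect: 1 + (5−1)·0.15 = 1.6.
- 42·1.6 = 67.2 (plan: 67).
- 67·1.10 = 73.7 (plan: 74).
- 74/5 = 14.8, so 15 centres per arm, or 75 workers.

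The arithmetic is sound. What is undefined is the time point to which it applies.

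**2. Move the proportions between horizons.** The documents give no departure pattern, so a constant departure hazard is assumed. The two proportions are treated as binary retention in the intervention and control arms, which is also an assumption. Then S(24) = S(12)².

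- If 0.90 and 0.65 are two-year values, the 12-month values are √0.90 = 0.949 and √0.65 = 0.806 (difference 14.2 points, ratio 1.18).
- If they are 12-month values, the two-year values are 0.90² = 0.81 and 0.65² = 0.4225 (difference 38.8 points, ratio 1.92).
- At their own horizon the difference is 25 points and the ratio 1.38.

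**3. Power of the binary comparison.** The effective number per arm is N/1.6: 67/1.6 = 41.9 and 75/1.6 = 46.9. Power = Φ{[|p1−p2|·√n − 1.96·√(2p̄(1−p̄))] / √(p1(1−p1)+p2(1−p2))}.

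| Case | Proportions compared | Power, 67 per arm | Power, 75 per arm | Workers per arm for 80% |
|---|---|---|---|---|
| Horizon matches | 0.90 vs 0.65 | 79% | 84% | 43·1.6 ≈ 69 |
| Two-year values, analysed at 12 months | 0.949 vs 0.806 | 51% | 56% | 82·1.6 ≈ 131 |
| 12-month values, analysed at two years | 0.81 vs 0.4225 | 97% | 98% | 24·1.6 ≈ 38 |

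**4. Proportion of days employed.** Under a constant hazard λ, the mean proportion over a window T is (1 − e^(−λT))/(λT).

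- If the stated figures are 12-month values: 0.949 vs 0.812 over 12 months (ratio 1.17) and 0.902 vs 0.670 over 24 months (ratio 1.35).
- If they are two-year values: 0.974 vs 0.900 over 12 months (ratio 1.08) and 0.949 vs 0.812 over 24 months (ratio 1.17).

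A relative risk built on this measure changes with the window in either case.

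**5. Cox model.** The hazard ratio is ln(0.90)/ln(0.65) = 0.24 at either horizon when hazards are constant. What changes is the expected number of departures. With 75 workers per arm there are about 34 by month 12 and 58 by month 24 if the figures are 12-month values, or about 18 and 34 if they are two-year values.

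**The case against.** The best defence is that the ascertainment section speaks of a main comparison. That wording gives 12 months precedence and leaves room for others. Monthly visits have no stated end, so a longer follow-up beside the 12-month comparison is possible. This lowers the risk of selective reporting but does not resolve the conflict, because no sentence says that two years is an extension and the individual-level retention models are described at no other horizon. Nor is this a detail that a condensed article leaves to a fuller plan: the article states both horizons.

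Other limits stand, and they rule out stronger readings.

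- A reader might infer that primary retention as a whole is analysed at two years. It is not: the cluster-level regression carries no two-year window and falls at 12 months under the ascertainment section.
- A reader might infer that the Cox model would give two different answers. Under constant hazards its hazard ratio is the same at both horizons, and only its precision differs.
- A reader might infer that the powered endpoint was a binary one, different from the proportion of days analysed. The sample-size section names no outcome, and its ICC rationale gives health worker days as an example of a process variable. A mismatch is therefore not shown.
- The 10% addition is for repeated satisfaction surveys, whereas retention comes from interviews with the clinical manager. Power for retention is therefore fairly shown up to 75 per arm, not only at 67.

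**Conclusion.** The point holds for the individual-level retention analyses. The abstract and the ascertainment section set 12 months, the analysis plan twice sets two years, and nothing ranks the two. The GEE relative risk, the proportion of days employed and the precision of the Cox model all depend on which section is followed. This must be corrected because it concerns a primary outcome and is contradictory as written.

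The power range of about 51% to 98% illustrates what the missing time point could mean. It rests on constant departure hazards, a binary retention endpoint, a design effect of 1.6 and 67 to 75 workers per arm. It does not show that the trial is underpowered: the documents do not say to which horizon 0.90 and 0.65 belong, and if that horizon matches the analysis, power is 79–84%, as planned.

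**What to change.** - Make 12 months, the document's own main comparison, the single primary horizon for retention. In the analysis plan, replace two years by 12 months in both places, and censor the Cox model at 12 months for the primary analysis.
- If follow-up to two years is intended, say so in the abstract, the ascertainment section and the analysis plan, and label that analysis secondary in each.
- In the sample-size section, state which outcome and which horizon 0.90 and 0.65 come from. They should not simply be relabelled as 12-month values. If they are not 12-month values, restate the power at 12 months.

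The Cox and GEE analyses can keep their present standing.

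The cost is wording and, at most, one power calculation; the 12-month choice needs no additional data. If the restated power is low, it has to be reported as such, because all 30 eligible centres in the district are already in the design.
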